#### Anesthesia management

During the preoperative visit, after signing the written consent, patients will be taught how to indicate postoperative pain based on a VAS, with levels ranging from 0 (no pain) to 10 (maximal pain). Patients will also be taught how to use the PCA device. In the operating theater, each patient will be prepared for monitoring of continuous blood pressure and heart rate, peripheral pulse oximetry, bispectral index (BIS system, Covidien/Medtronic, Minneapolis, MN, USA), and electrocardiography. Then a peripheral venous cannula will be inserted and an intravenous (IV) infusion of crystalloid solution will be started. Each participant will be premedicated with an IV infusion of midazolam 0.03 mg/kg before the induction of general anesthesia. A standard general anesthesia protocol will be followed, using 0.3–0.4 μg/kg sufentanil, 1.5–2 mg/kg propofol, and 0.2 mg/kg cisatracurium or 0.6 mg/kg rocuronium. Anesthesia will be maintained with IV administration of propofol and remifentanil, and muscle relaxation will be maintained using IV cisatracurium or rocuronium. After endotracheal intubation, invasive blood pressure will be monitored by placing an arterial line if deemed necessary by the anesthesiologist in charge. Ventilation will be adjusted as needed to maintain normocapnia. Anesthesia will be maintained with IV propofol and remifentanil, and muscle relaxation will be maintained using IV cisatracurium or rocuronium. Local infiltration of the prepared solution will be performed by the neurosurgeon, before the incision is made. Sufentanil will be administered at certain time points to attenuate potent stress responses and maintain the mean arterial pressure and heart rate fluctuations within a 20% range of baseline. No additional analgesics will be administered intraoperatively. Antihypertensive drugs or vasoactive drugs will be administered as needed, and crystalloid and colloid solutions will be infused as necessary, by the anesthesiologist in charge. All intraoperative physical parameters, fluid input and output, and dosage of all drugs will be closely monitored and recorded.

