### Outcomes {12}

Clinical and demographic characteristics such as gender, age, weight, BMI, ASA status, type of surgery (laminoplasty or laminectomy), level of spine to be treated (cervical, thoracic, lumbar, or sacral), number of levels to be treated (1, 2, 3, 4 levels or more than 4 levels), and Oswestry Disability Index (ODI) will be recorded. After the operation, the duration of surgery, length of incision (in millimeters), and volume of local anesthesia (in milliliters) injected for preeemptive infiltration will be recorded. Postoperative complications such as postoperative pain due to spinal cord or nerve injury, wound infection, wound hematoma, delirium, serious adverse effects, and death may affect the follow-up process. Other complications such as allergic reaction, local or systemic toxicity, changes in wound healing, or increased wound drainage will be closely monitored.

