### Postoperative follow-up data recording

Follow-up will be conducted on day 3, at weeks 1, 2, 4, and 6, and at months 3 and 6 by an experienced research member blinded to the study. All the participants will complete a 6 months’ follow-up. The postoperative follow-up data recording parameters will also include VAS and PSS.

World Health Organization Quality of Life-BREF (WHOQOL-BREF) scores will be used to obtain scores for four domains related to quality of life: physical health (7 items), psychological (6 items), social relationships (3 items), and environment (8 items). This assessment will also include two stand-alone questions on overall quality of life and satisfaction with health. Each question will be rated on a scale of 1–5, with higher scores signifying better quality of life.

Functional disability will be assessed preoperatively and at 4 and 6 weeks and 3 and 6 months after surgery using the ODI. The ODI includes 10 questions about pain and activities of daily living. Each item has five response categories, ranging from no pain-related disability (0), to the worst possible pain-related disability (100).

The Patient and Observer Scar Assessment Scale (POSAS), comprised of subjective symptoms of pain and pruritus, will be assessed at 6 months postoperatively.

AEs such as nausea, vomiting, and steroid-related adverse effects (gastrointestinal bleeding, gastritis, delayed wound healing, etc.) will be documented for comparison of outcome.

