### Secondary outcomes

The secondary outcomes are as follows:
VAS_M_ and VAS_R_ 2 h, 4 h, 8 h, 24 h, 48 h, 72 h, 1 week, 2 weeks, 4 weeks, 6 weeks, 3 months, and 6 months after surgeryCumulative butorphanol dose for four separate periods (0–4, 4–8, 8–24, and 24–48 h), a total press count including both valid and invalid presses, first analgesia demand on the PCA devicePSS 2 h, 4 h, 8 h, 24 h, 48 h, 72 h, 1 week, 2 weeks, 4 weeks, 6 weeks, 3 months, and 6 months postoperativelyPONV and RSS scores 2 h, 4 h, 8 h, 24 h, and 48 h after surgeryWHOQOL-BREF scores preoperatively and 6 months postoperativelyFunctional disability assessed by ODI scores preoperatively and at 4 weeks, 6 weeks, 3 months, and 6 months after surgeryWound healing situation assessed by the POSAS scores at 6 months postoperatively.

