### Sample size {14}

Ersayli et al. reported that total morphine consumption at 24 h was 13.2 ± 4.1 mg after lumbar discectomy for patients who received local wound infiltration of bupivacaine alone just before incision [14]. The analgesic effect of 1 mg morphine is the same as that of 3.75–7 mg butorphanol. This dose of morphine could be converted into an equianalgesic dose of butorphanol (with conversion factor 1 mg morphine = 3.75–7 mg butorphanol). Therefore, we have estimated that total butorphanol consumption will be about 120.0 ± 90.0 mg at 48 h after laminoplasty or laminectomy for the patients who received preemptive analgesia with local anesthetics.

Nakai et al. suggested that local wound infiltration by addition of betamethasone could reduce the dose of analgesics by about 45% in the 24 h after lumbar discectomy [18]. Therefore, we hypothesize that the cumulative butorphanol consumption during the 48 h after lumbar discectomy will be 120.0 ± 90.0 mg in the control group and 70.0 ± 50.0 mg in the treatment group. Based on a 90% power with a two-sided α of 0.05 and a dropout rate of 20%, we have calculated that at least 116 patients (58 per group) will be required.

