## Discussion

This trial will be a PROBE study. It will have better application in routine clinical practice, along with the clinical outcomes of a large simple research, which will permit a broader patient population and will include the advantage of randomization and an extensive evaluation of endpoints by blinded experts [19]. To our knowledge, there has been no attempt in the past to infiltrate laminoplasty or laminectomy with a preemptive local administration of betamethasone and ropivacaine. This study will add significant new knowledge to the effect and feasibility of preemptive wound infiltration of betamethasone.

Due to its large particles occluding the blood vessels supplying the spinal cord, betamethasone was previously reported to result in infarction of spinal cord after epidural analgesia [20]. However, we speculate that local peri-incisional infiltration of betamethasone is safe, as betamethasone has previously been used for intralesional [21], local infiltration [22], intramuscular [23], and intra-articular injections [16]. Local infiltration of steroid hormones will undeniably present the risk of delayed wound healing or local infection. However, we intend to use the lowest possible concentration of betamethasone for local infiltration based on the previous literature [15, 16, 22, 24], and thus this concentration should be considered safe. Wound healing and infection will be closely observed. The study will be immediately terminated in case of serious adverse reactions by the PRE-EASE Trial Management Group.

There are still some limitations regarding our study. Firstly, this is a single-center study; a multicenter study would be helpful in providing more significant data. In addition to incisional pain, acute pain after laminoplasty or laminectomy may be followed by long-term chronic pain that may not only originate from the incisional wound, but may also include neuropathic pain from spinal cord damage and nerve root injury. Another possible limitation of this study is that it will only involve infiltration of the surrounding tissue of the incision site. Therefore, we would like to suggest a further detailed study, regarding whether local betamethasone injection into the affected nerve roots before closure could be beneficial for postoperative pain after laminoplasty or laminectomy.

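### No preoperative VAS is scheduled, so the first-listed secondary outcome cannot be adjusted for, or compared with, its own baseline; preoperative pain is captured only indirectly, through the ODI

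*Protocol article*

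**What the plan says.** Four places in the protocol article agree.

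- **Anesthesia management.** After consent, "patients will be taught how to indicate postoperative pain based on a VAS". This is training; no score is mentioned. The oversight section describes the same teaching.
- **Outcomes {12}.** The baseline characteristics run through demographics, ASA status, type of surgery, spinal level and number of levels, "and Oswestry Disability Index (ODI) will be recorded". No pain score is named.
- **Secondary outcomes.** The first item is "VAS_M_ and VAS_R_ 2 h, 4 h, 8 h, 24 h, 48 h, 72 h, 1 week, 2 weeks, 4 weeks", continuing to 6 weeks, 3 months and 6 months. Every time is postoperative.
- **Table 1.** Both VAS rows start at 2 h. The Preoperative column is marked for ODI and WHOQOL-BREF but not for VAS.

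On the ODI, the follow-up section states: "Functional disability will be assessed preoperatively and at 4 and 6 weeks and 3 and 6 months after surgery using the ODI". It adds: "The ODI includes 10 questions about pain and activities of daily living".

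**The concern.** The operations treat conditions such as stenosis, disc herniation and intraspinal lesions, so some patients will plausibly be in pain before surgery. The exclusion criteria remove chronic opioid users and users of analgesic drugs, but not patients in pain as such.

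The abstract asks about long-term as well as short-term effects, and the Discussion notes that "acute pain after laminoplasty or laminectomy may be followed by long-term chronic pain". A reader of the 6-month results will want to know whether a score of, say, 3 is better than, equal to or worse than where the patient began. Without a preoperative score on the same scale, that comparison cannot be made.

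Baseline pain would also be a natural covariate for the later scores, and the most direct check on whether the arms started alike. Patients are already taught the scale before surgery, so the score is omitted at a visit where it would be easy to take. Once the operation has happened it cannot be recovered, and no analysis plan could supply it later.

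**Working it through.** **1. Does the gap touch the sample size?** Inputs from Sample size {14}: "120.0 ± 90.0 mg in the control group and 70.0 ± 50.0 mg in the treatment group", power 90%, two-sided α 0.05, dropout 20%.

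- Root mean square SD = √((90² + 50²)/2) = √5300 = 72.8 mg; difference = 50 mg.
- Normal approximation: n = 2 × (1.960 + 1.282)² × 5300 / 50² = 44.6, so 45 per group. Then 45/0.8 = 56.25, so 57 per group, 114 in total.
- Calculation based on the t distribution: 46 per group. Then 46/0.8 = 57.5, so 58 per group, 116 in total.

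The stated 116 reproduces. It rests on butorphanol dose alone, so a missing VAS baseline does not change it.

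**2. What would adjustment for baseline VAS gain?** The protocol gives no correlation r between baseline and follow-up VAS, so r is an assumption. Analysis of covariance multiplies residual variance by 1 − r². The equivalent sample-size factor, against no covariate, is 1/(1 − r²). The difference detectable at 80% power, in SD units, is (1.960 + 0.842) × √(2/n) × √(1 − r²). With n = 46 evaluable per group:

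| Assumed r | Variance factor | Sample-size factor | Detectable difference |
|---|---|---|---|
| 0 | 1.00 | 1.00 | 0.58 SD |
| 0.3 | 0.91 | 1.10 | 0.56 SD |
| 0.5 | 0.75 | 1.33 | 0.51 SD |

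With all 58 per group the detectable difference goes from 0.52 SD to 0.50 SD (r = 0.3) or 0.45 SD (r = 0.5).

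**3. How large could a chance imbalance in baseline VAS be?** Its standard error is √(2/n) in SD units: 0.19 for n = 58 and 0.21 for n = 46. The 95% ranges are ±1.96 times these, about ±0.36 SD and ±0.41 SD. At r = 0.5, an imbalance of 0.36 SD would move the follow-up difference by 0.5 × 0.36 = 0.18 SD. This describes how far a single trial may stray by chance. The average over randomisations is zero, and the usual standard error already covers it.

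**4. Does the ODI fill the gap?**

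| | VAS | ODI |
|---|---|---|
| Preoperative | no | yes |
| 2 h to 2 weeks | yes | no |
| 4 and 6 weeks, 3 and 6 months | yes | yes |
| Content | pain intensity, rest and movement scored separately | pain and daily activities combined |

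The ODI provides a pain-related baseline with matching late follow-up. It does not separate rest from movement, and it is not on the VAS scale.

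**The case against.** The strongest reply is that pre-existing pain is not unmeasured. The preoperative ODI asks about pain, can reveal an imbalance and can serve as a covariate. That stands. A reader might infer from the missing VAS that pre-existing pain cannot be adjusted for at all, or that a chance imbalance would be invisible. The documents do not support either reading. What is missing is adjustment on the outcome's own scale.

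Second, a reader might infer that the VAS comparisons are biased. They are not, in expectation: allocation is random, and no outcome is defined as change from baseline VAS or as incidence of new chronic pain.

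Third, the gain in the working is measured against no covariate. The relevant figure is the gain beyond the ODI, which cannot be computed from the document and would probably be smaller. The correlation is also likely to be weaker in the first 48 h, when patients titrate their own butorphanol. Both points stand.

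Fourth, a reader might expect a baseline VAS to separate new from persisting pain. It would do so only partly. The Discussion names several possible sources of later pain, and the scale as described records no site or origin, so an equal score at 6 months could hide a change of source.

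Finally, the baseline list in Outcomes {12} is worded as illustrative, Table 1 has a general baseline-data row, and covariate choice may sit in an analysis plan that is not shown. The absence of a named covariate is therefore no fault. But the schedule marks other instruments before surgery and leaves VAS unmarked, which is a feature of data collection and not an omitted analysis detail.

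**Conclusion.** The point holds as a limited one. No preoperative VAS is scheduled, so two things are lost on the first-listed secondary outcome: adjustment for its own baseline, and comparison of late scores with the patient's preoperative level on the same scale.

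The size is modest: a 9% to 25% reduction in residual variance forgone relative to no covariate. That rests on an assumed correlation of 0.3 to 0.5 and 46 evaluable patients per group. How many enrolled patients will have preoperative pain is not stated and is not assumed here. The validity of the randomised comparison, the primary outcome and the sample size are all untouched. The case for acting is that the remedy is cheap and the information cannot be recovered after surgery.

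**What to change.** - Score VAS at movement and at rest at the preoperative visit, when the scale is taught, and mark both rows in the Preoperative column of Table 1.
- Use the corresponding baseline VAS as a covariate in the VAS analyses.
- Report VAS at 3 and 6 months alongside the baseline values.
- For patients already enrolled without a baseline score, use the preoperative ODI as the covariate.

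The cost is two form fields at an existing visit, one covariate per analysis and a protocol amendment. The limit should be stated in the report: a baseline VAS shows the level of earlier pain and does not identify the origin of later pain.

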#### Additional interventions

The ongoing continuous infusion of propofol and remifentanil will be stopped right after the suture of the incision. To prevent postoperative nausea and vomiting, 8 mg of ondansetron will be administered. Any residual muscle relaxation will be antagonized by atropine and neostigmine. Once the patient is hemodynamically stable, along with the recovery of adequate spontaneous ventilation and satisfactory neurological evaluations, the patient will be extubated and transferred to a post-anesthesia care unit. A PCA device containing 10 mg butorphanol tartrate injection (HengRui Medical Co., Ltd., Lianyungang, Jiangsu, China) and 10 mg tropisetron hydrochloride injection (Southwest Pharmaceutical Co., Ltd., Chongqing, China) diluted to a total volume of 100 ml with 0.9% normal saline, will be connected to the patients, for a total duration of 48 h. Apon® electronic infusion pumps (ZZB-I-150, Apon Medical Technology Co., Ltd., Jiangsu, China) will be used for patient-controlled analgesia (PCA). The PCA device will have a bolus dose of butorphanol set at 0.3 mg with a lockout interval of 15 min. Both the initial dose and background infusion of the PCA device will be set at zero. The participants will be advised to push the analgesic demand button when they feel pain. Each press will be recorded by an electronic memory system, including both valid and invalid presses. Invalid presses refer to presses for bolus during the lockout period. In case of inadequate analgesia four times after the butorphanol bolus, the bolus dose would be increased gradually with the final maximum dose not exceeding 4 mg per hour. There will be real-time updates of drug dosage, press counts, and time of each press to the iPainfree online recording system. Participants will be allowed to take oral supplementary acetaminophen 500–1000 mg every 4 to 6 h if necessary after 48 h, until the end of our study.

### Criteria for discontinuing or modifying allocated interventions {11b}

A detailed recording of all adverse events (AEs) throughout the course of the study will be properly recorded, closely monitored, and reported to the ethics committee as soon as possible, with the intentions of a resolution or stabilization, or even termination of the study if necessary.

### Strategies to improve adherence to interventions {11c}

During the study, periodic monitoring will be conducted by a blinded research member, who will visit each patient in person at 2, 4, 8, 24, and 48 postoperative h, for the recording of postoperative parameters and to ensure adherence to interventions. The blinded postoperative care nurses of the neurosurgical department will be checking on patients from time to time and will advise them to press the analgesic demand button on the PCA device if necessary. Preoperatively, the patients will have been instructed on how to use the PCA device after their written consent is obtained. Both groups will have the PCA device bolus dose of butorphanol set at 0.3 mg with a lockout interval of 15 min, with the background infusion set to zero. There will be real-time updates of drug dosage, press counts, and time of each press, which will also help with monitoring and improving adherence. After the initial 48-h postoperative period and until the end of the study, patients will be allowed to take oral supplementary acetaminophen 500–1000 mg every 6 h if necessary. Follow-up will be conducted on day 3, at weeks 1, 2, 4, and 6, and at months 3 and 6 by a blinded research member.

### Relevant concomitant care permitted or prohibited during the trial {11d}

In the immediate 48-h postoperative period, all participants will be provided with a butorphanol tartrate and tropisetron hydrochloride intravenous PCA device. After 48 h the participants will be allowed to take oral supplementary acetaminophen 500–1000 mg every 4 to 6 h if necessary, until the end of the 6 months’ follow-up period.

### Provisions for post-trial care {30}

There is no anticipated harm and compensation for trial participation.

### Outcomes {12}

Clinical and demographic characteristics such as gender, age, weight, BMI, ASA status, type of surgery (laminoplasty or laminectomy), level of spine to be treated (cervical, thoracic, lumbar, or sacral), number of levels to be treated (1, 2, 3, 4 levels or more than 4 levels), and Oswestry Disability Index (ODI) will be recorded. After the operation, the duration of surgery, length of incision (in millimeters), and volume of local anesthesia (in milliliters) injected for preeemptive infiltration will be recorded. Postoperative complications such as postoperative pain due to spinal cord or nerve injury, wound infection, wound hematoma, delirium, serious adverse effects, and death may affect the follow-up process. Other complications such as allergic reaction, local or systemic toxicity, changes in wound healing, or increased wound drainage will be closely monitored.

### Postoperative recording parameters for up to 48 h

The parameters will be recorded at 2, 4, 8, 24, and 48 h after surgery by a research member, who will visit each patient in person. Pain scores will be measured using the VAS score: an 11-point VAS score during movement (VAS_M_) and at rest (VAS_R_) will be recorded, with 0 indicating no pain and 10 indicating the most severe pain imaginable.

Time of first analgesic demand will be indicated by the first press of the analgesic demand button on the PCA device. The time of first analgesic demand, total press count, the cumulative butorphanol dose for four separate periods (0–4, 4–8, 8–24, and 24–48 h), and total butorphanol dose at 48 h will be recorded.

The Patient Satisfaction Score (PSS) used in this study will comprise points 1–4, based on the study by Mobbs et al. [17].

Postoperative nausea and vomiting (PONV) and Ramsay Sedation Scale (RSS) scores will also be recorded. PONV will be measured using an ordinal scale with the following values: 0 no nausea, 1 mild nausea not requiring treatment, 2 nausea requiring treatment, 3 vomiting. The RSS uses a 6-point scale to assess sedation levels, with 1 indicating agitated, anxious; 2 cooperative; 3 only responds to commands; 4 strong response to glabellar tapping or noisy stimulants; 5 weak response to glabellar tapping or noisy stimulants; 6 no response.

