### Participant timeline {13}

The enrollment, interventions, assessments, and study visits of the PRE-EASE trial are presented in Table 1.

**Table 1 Tab1:** Study visits of the PRE-EASE trial

	Study period															
	Enrollment	Allocation	Post-allocation													
Time points	Preoperative	0 day (d)	Surgery	2 h	4 h	8 h	1 d	2d	3d	1 week (w)	Discharged	2w	4w	6w	3 months (m)	6 m
Enrollment																
Eligibility screening	X															
Informed consent	X															
Random allocation		X														
Interventions																
Betamethasone plus ropivacaine		X														
Ropivacaine		X														
Assessments																
Baseline data	X	X	X													
Intraoperative data			X													
Cumulative butorphanol consumption					X	X	X	X								
Patients with no butorphanol								X								
Total PCA button press count								X								
Time of first analgesia demand					X	X	X	X								
VAS_M_				X	X	X	X	X	X	X		X	X	X	X	X
VAS_R_				X	X	X	X	X	X	X		X	X	X	X	X
PSS				X	X	X	X	X	X	X		X	X	X	X	X
PONV				X	X	X	X	X								
RSS				X	X	X	X	X								
WHOQOL-BREF	X															X
ODI	X												X	X	X	X
POSAS																X
AEs																
Nausea				X	X	X	X									
Vomiting				X	X	X	X									
Gastritis				X	X	X	X									
GI bleeding				X	X	X	X									
Delayed wound healing				X	X	X	X									

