### Statistical methods

#### Statistical methods for primary and secondary outcomes {20a}

Statistical analyses will be performed using the statistical package SPSS software 25.0. A Kolmogorov-Smirnov test will be used to assess normality of variables. Data for normal distribution will be presented as mean ± SEM (standard error of the mean). Variables for skewed distributions will be described as median and interquartile range (IQR). Categorical variables will be expressed as frequencies with percentages.

Comparisons between the groups will be carried out using an independent *t* test to compare normally distributed data, the Mann-Whitney *U* test for skewed data, and a χ^2^ test or Fisher’s exact test to compare categorical data such as safety analyses with the incidence of AEs. For numerical data collected at different time points throughout the course of 6 months (e.g., PCA cumulative consumption of butorphanol, PONV, RSS, PSS, and ODI), repeated measures analysis of variance will be performed between the two groups. The significance level will be set at *P* < 0.05.

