#### Methods in analysis to handle protocol non-adherence and any statistical methods to handle missing data {20c}

All researchers will be trained referring to the same training protocol. Protocol modifications will not be expected. Missing intraoperative data, if any, will be obtained from the electronic hospital files. Postoperative evaluation at specified time points is mandatory, and missing postoperative data are not to be anticipated. Analyses of all outcomes will be performed according to the intention-to-treat principle, and once enrolled, all participants will be analyzed, regardless of the findings.

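### Time to first analgesic demand is a time-to-event outcome over 48 h, but the named tests give patients who never press no value and no censoring rule

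*Protocol article*

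**What the plan says.** All references are to the protocol article.

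- **Definition.** Postoperative recording parameters for up to 48 h: "Time of first analgesic demand will be indicated by the first press of the analgesic demand button on the PCA device". Secondary outcomes lists first demand on the PCA device.
- **Window.** Additional interventions: the device "will be connected to the patients, for a total duration of 48 h".
- **No automatic dosing.** Same section: "Both the initial dose and background infusion of the PCA device will be set at zero". Barring device failure, a patient with no butorphanol is therefore one who never pressed.
- **Non-users foreseen.** Table 1, under Participant timeline {13}, has a row "Patients with no butorphanol", marked at day 2.
- **Tests.** Statistical methods {20a}: "Comparisons between the groups will be carried out using an independent" t test "to compare normally distributed data, the Mann-Whitney *U* test for skewed data", with chi-square or Fisher for categorical data. Repeated measures ANOVA is reserved for data collected at several time points. No survival method is named.
- **Missing data and analysis set.** Section {20c} states that "missing postoperative data are not to be anticipated" and also that "once enrolled, all participants will be analyzed, regardless of the findings".

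**The concern.** A time to first press exists only for patients who press. Section {20a} does not name this outcome, but its general rule assigns tests by data type. One time in hours per patient is numerical, so it falls to the t test or the Mann-Whitney test. Both need a number for every patient, and never-pressers have none. The analyst must then leave them out or invent a value, and the plan covers neither.

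Whether a patient presses is known only after randomisation. Under the trial's hypothesis, more treated patients should get through 48 h without asking for analgesia. A comparison limited to pressers is no longer between the randomised groups, and it can miss a benefit that consists of avoiding any request.

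**Working it through.** **1. The plan's own figure.** No figure is given for this outcome, so the only one to reproduce is the sample size, which supplies the 58 per arm used below. Inputs from Sample size {14}: 120 ± 90 mg against 70 ± 50 mg, 90% power, two-sided 0.05, 20% dropout.

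- Common SD = √[(90² + 50²)/2] = √5300 = 72.8 mg; difference = 50 mg.
- Power with the noncentral t (equal-variance form): 0.897 at 45 per arm and 0.903 at 46, so 46 are needed.
- 46/(1 − 0.20) = 57.5, rounded up to 58 per arm, 116 in total. This agrees with the protocol.

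**2. Do the stated rules fit together?** For a patient who never presses:

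| Rule | Consequence |
|---|---|
| Definition by first press | no value |
| t or Mann-Whitney on recorded values | patient drops out |
| All participants analysed {20c} | patient must stay in |
| No missing postoperative data expected {20c} | no substitution rule |

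The rules cannot all be followed for this patient unless something is added.

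**3. Size, by simulation.** 58 per arm; exponential time to first press; a share in each arm who never press; observation ends at 48 h; 3,000 simulated trials per row; two-sided 0.05. The shares and medians are assumptions, because the documents give none. Entries are the percentage of trials that reject.

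| Never press, control / treatment | Median among pressers, control / treatment | Mann-Whitney, dropped | t, dropped | Mann-Whitney, tied at 48 h | Log-rank, censored at 48 h |
|---|---|---|---|---|---|
| 5% / 5% | 4 h / 4 h | 5 | 5 | 5 | 5 |
| 5% / 15% | 4 h / 4 h | 5 | 5 | 15 | 29 |
| 5% / 25% | 4 h / 4 h | 4 | 5 | 48 | 77 |
| 10% / 30% | 4 h / 4 h | 5 | 5 | 46 | 69 |
| 5% / 25% | 4 h / 6 h | 39 | 49 | 90 | 96 |
| 2% / 5% | 4 h / 6 h | 44 | 54 | 53 | 60 |

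When the whole benefit lies in never pressing, dropping those patients leaves only the 5% null rate. When nearly everyone presses (last row), the methods differ little.

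**4. How large can the never-press share be?** A never-presser has a dose of 0 mg. For a non-negative variable, the share above zero is at least mean²/(mean² + SD²). With the protocol's 70 ± 50 mg for the treatment arm, that is 4900/(4900 + 2500) = 4900/7400 = 66%, so at most 34% can be zero. At 30% zeros, pressers would average 70/0.7 = 100 mg with SD √(7400/0.7 − 100²) = √571 ≈ 24 mg. The 10% / 30% row is therefore close to the most that the protocol's own planning figures allow, and the 5% / 15% row is more moderate.

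**The case against.** **This is detail for an analysis plan.** Section {20a} is two paragraphs of a journal article, and a censoring rule for one secondary outcome is often set elsewhere. That is fair for the missing rule alone. But the article does state which tests will be used and when, and by that rule this outcome goes to tests that do not suit it.

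**Mann-Whitney can keep everyone.** With a common 48 h window, never-pressers can be tied at the top rank, which gives a valid test. This stands: the plan's menu is not blind to the effect. The protocol does not say that this will be done, the t test has no comparable remedy, and under the 10% / 30% assumption the tied version rejects in 46% of trials against 69% for log-rank.

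**A reader might infer that the plan excludes never-pressers and breaches intention to treat.** The documents do not support that. No sentence excludes them, and {20c} says all are analysed. Exclusion is only what happens by default when a test meets an absent value.

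**A reader might also infer that the trial would lose the benefit it is looking for.** It would not. Never-pressers count as 0 mg in the primary outcome and as zero in the total press count. Table 1 counts them directly, and Fisher's test, already in the plan, rejects in about 72% of trials on that count at 10% / 30%.

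**No press does not prove complete analgesia.** Sedation, delirium or a device problem could also explain it. And ward nurses will prompt patients to press (Strategies to improve adherence {11c}), which favours low never-press shares. Both points stand and limit the likely size.

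**Conclusion.** The point holds in a limited form. The tests fixed in {20a} do not suit an outcome defined as the time to an event within 48 h, and the plan does not say how patients without the event enter the comparison. The effect on power ranges from near total (about 5% against 69% if never-pressers are dropped at 10% / 30% with equal timing) through moderate (46% against 69% if they are tied at 48 h) to small when almost everyone presses.

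These figures rest on assumed never-press shares, exponential times and 58 analysed per arm. They also rest on the inference that the general rule for numerical data governs this outcome. One secondary outcome is affected. The primary outcome and the 116 patients are untouched.

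**What to change.** In Statistical methods {20a}, state that time to first analgesic demand:

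- runs from a stated time zero, for example connection of the PCA device;
- is described by Kaplan-Meier curves and compared by log-rank;
- includes all randomised patients, with never-pressers censored at 48 h or at PCA disconnection if earlier.

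A Cox hazard ratio is optional and should be unadjusted, since the protocol names no covariates for its primary analysis. Report the Table 1 count of patients without butorphanol per arm, with a risk difference and 95% CI.

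The cost is a short addition to the text and a little more analysis. No new data are needed, because the pump already logs the time of each press; the connection and disconnection times must be kept with that log.
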